## Abstract

**Background: **Tongue tumors show intra and inter-tumoral heterogenicity with high incidence, relapse and mortality rates necessitating further research.  Recurrence/metastasis that occurs  after surgical resection of primary cancer is often the reason for poor survival in these patients.  Lymph nodes are the most common site of metastasis in tongue tumors. Therefore, premetastatic molecular changes can be best evaluated in lymph nodes which may epitomize the earliest events in the metastasis cascades. The presence of circulating tumor cells(CTCs) in the absence of nodal disease (N0) may represent tumor aggressiveness, suggesting an immune escape which may have high metastatic potential. This trial  was developed  to investigate the earliest pre-metastatic changes which may regulate tumor dormancy and predict metastasis. A better understanding of organotropism or pre-metastatic changes can help in theragnostic, thereby  preventing the outbreak of overt metastasis.

**Methods:** A single-institutional prospective observational cohort study. This trial will be conducted at a tertiary care Centre (Amrita Institute of Medical Sciences Kochi).  Eligible patients will be enrolled after obtaining informed consent. The dissected lymph nodes will  be subjected to histopathological and immunohistochemical analyses for premetastatic niche (PMN) formation. In addition, circulating tumor cells will be evaluated before treatment and 6 months after treatment. The patients will be followed  up for a period of two years to correlate the findings with the recurrence-free survival.

**Expected results:**  The pre-metastatic changes, if detected will  be  a predictive biomarker. It may help to define future drug targets for metastasis chemoprevention   . CTCs may  define the tumor aggressiveness ,there by  prognostication  and helps in better disease management.

**Ethics and dissemination:** The study has received the following approval:

Ethics Committee of Amrita School of Medicine (ECASM-AIMS-2022-048).Trial Registered Prospectively( CTRI/2022/03/041256 ) on 22/03/2022 under Clinical Trial Registry of India

AbbreviationsCK8/18/19Cytokeratin 8/18/19CTCCirculating Tumour CellsCTMCirculating Tumour Micro emboliDAMPDamage-associated molecular patternECSExtra capsular SpreadEMTEpithelial -Mesenchymal TransitionEpCAMEpithelial cell adhesion moleculeFFPEFormalin fixed -paraffin embeddedIHCImmuno HistochemistryLNLymphnodeLOX 2Lysyl Oxidase 2MDSCsMyeloid-derived suppressor cellsOSCCOral Squamous Cell CarcinomaOTSCCOral Tongue Squamous Cell CarcinomaPMNPremetastatic NicheSTAT 3Signal Transducer and activator of transcription3VEGF AVascular Endothelial Growth Factor A

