### Eligibility criteria

Eligibility criteria are summarised in
Table 1.

**Table 1. T1:** Inclusion & Exclusion Criteria.

Inclusion criteria	Exclusion criteria
Age- 18-80 years OTSCC patient reporting to this center without any previous tumour treatment history other than diagnostic biopsy.	Other subsites of oral squamous cell carcinoma.
Curative intent surgery as a primary modality of treatment with neck dissection.	OTSCC indicative of only wide local excision (not indicative of neck dissection).
T 1 to T4 with and without nodal metastasis and willing to sign the Informed Consent.	Secondary primary tumors or recurrent tumours.
Patients who agree to complete the treatment as per standard treatment protocol and routine follow-up visits.	OTSCC patients on neoadjuvant chemotherapy.

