### Study implementation/methodology

Patient inclusion is done based on the inclusion criteria. The trial will enroll 97 eligible patients. After obtaining written informed consent, blood samples and tissue biopsy blocks will be collected from them.

For CTC/CTM evaluation – Blood samples with minimum trauma will be collected before and 6 months after surgery. 5 mL of peripheral whole blood samples will be collected in 10-mL vacutainer tubes (Becton Dickinson, New Jersey). The blood samples will be stored in the refrigerator at 2 to 8
^0^ C. CTCs will be isolated by using Drugs Controller General of India (DCGI) approved OncoDiscover liquid biopsy technology. The OncoDiscover CTC isolation technique uses multifunctional, iron oxide-based, magneto-polymeric, and anti-epithelial cell adhesion molecule (EpCAM) targeting superparamagnetic nanoparticles.
^
10
^ Enumeration of CTC is based on CD45-, EpCAM+ and CK8,CK18 &CK19+ expression. CTM clusters are a group of two or more aggregated CTCs. The number of CTCs positive for PD-L1 expression is also evaluated.

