### Primary outcomes

•The correlation of molecular expression of STAT 3, LOX 2, and VEGF in the premetastatic nodes (-ve N) with recurrence -free survival. These markers will be correlated individually. This will allow us to analyse the significance of premetastatic niche formation and the pathways leading to it.•To correlate the presence of CTC/CTM at two different time points to recurrence-free survival. This will allow us to establish the role of liquid biopsy in prognostication ie. the presence of CTC as a predictor/indicator of tumor spread via blood or lymphatic channels.•The evaluation of Stat3 expression in tissue and PD- L1 in CTC will reveal on the local and systemic immune status of patients respectively. Those PD-L -1positive CTCs may be a strong indicator of those exceptional CTCs that escape the immune surveillance mechanism.

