### Participation timeline

All subjects will be part of the trial for two years post initiation of the treatment or till the time when they show progressive incurable disease.

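### The second CTC/CTM draw is timed from treatment in the Abstract and from surgery in the Methods: use one anchor, and analyse that sample from its actual draw date

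*Protocol article*

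**What the plan says.** Two places in the protocol article time the second blood sample. The Abstract states: "circulating tumor cells will be evaluated before treatment and 6 months after treatment". The Methods, under Study implementation/methodology, state: "Blood samples with minimum trauma will be collected before and 6 months after surgery".

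The sample is used in the second item under Primary outcomes: "To correlate the presence of CTC/CTM at two different time points to recurrence-free survival". That item does not restate the time points. The Introduction places the CTC/CTM aim differently, as a secondary objective in N0 patients.

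Three eligibility criteria bear on what treatment covers. One reads "Curative intent surgery as a primary modality of treatment with neck dissection", another "Patients who agree to complete the treatment as per standard treatment protocol and routine follow-up visits", and the stage range is "T 1 to T4 with and without nodal metastasis and willing to sign the Informed Consent". The Participation timeline keeps subjects in the trial for "two years post initiation of the treatment", or until progressive incurable disease. The Statistical analysis plan section names Kaplan-Meier and log-rank methods for disease-free survival.

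**The concern.** Surgery is described as the primary modality, and a separate criterion asks patients to complete a standard course. Treatment can therefore be read as something longer than the operation. For a patient who has surgery alone, the Abstract and the Methods give the same date. For a patient treated further after surgery, they may not, and the Abstract does not say from which point it counts.

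The study takes only one sample after surgery, and Methodological issues concedes that more frequent sampling is lacking. The date of that draw therefore decides which patients are still recurrence-free when sampled.

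A related hazard does not depend on the anchor. Suppose RFS is counted from treatment and patients are grouped by their second-sample CTC status. Recurrences before the draw would then be credited to a measurement taken after them, and a positive count could reflect the recurrence rather than foretell it. Patients who left the trial with incurable disease before the draw would have no second sample. Those sampled while recurrence-free would carry about six months in which, by construction, they could not have had an event.

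**Working it through.** **The passages side by side**

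- Abstract: six months after treatment, with neither start nor end specified.
- Study implementation/methodology: six months after surgery.
- Participation timeline: counts trial membership from initiation of treatment and does not time the draw. Earlier tumour treatment and neoadjuvant chemotherapy are excluded, so initiation of treatment fits the surgery date.

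The anchors coincide if treatment is the surgery, or is counted from its start. They separate only if treatment continues after surgery and the Abstract means after its end.

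**The plan's own figure.** n = z²pq/d² = 1.96² × 0.5 × 0.5 / 0.10² = 96.04, rounded up to 97. It reproduces and does not depend on the draw date. It is used below only as the denominator.

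**Recurrences before the draw**

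Inputs: 20-30% recurrence within 12 months, from a tongue cancer study cited in the Discussion; 97 patients. Assumptions: that rate applies to this cohort, and the hazard is constant.

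λ = -ln(1 - r12)/12, and cumulative recurrence at month t is 1 - exp(-λt). Months 8 and 10 correspond to treatment ending 2 or 4 months after surgery. That gap is an assumption, because the documents give none.

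| 12-month recurrence | λ per month | month 6 | month 8 | month 10 |
|---|---|---|---|---|
| 20% | 0.0186 | 10.6% | 13.8% | 17.0% |
| 30% | 0.0297 | 16.3% | 21.2% | 25.7% |

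- By month 6 after surgery: 97 × 0.106 ≈ 10 to 97 × 0.163 ≈ 16 patients. These precede the draw under both anchors.
- Extra recurrences before a later draw: about 3 to 6 percentage points (20% case) or 5 to 9 points (30% case). They arise only in patients treated after surgery, whose share is not stated.

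**Effect of early clustering.** The Discussion also cites recurrence as very frequent in the first six months. With the 12-month total held at 20-30%, front-loading would raise the month-6 figure but leave fewer events between months 6 and 10. The 3-9 point difference between anchors would shrink.

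**Events left for a landmark analysis.** Carrying the constant hazard on to 24 months (a further assumption, with no loss to follow-up), cumulative recurrence is 1 - 0.8² = 36% or 1 - 0.7² = 51%, about 35 or 49 of 97. After a month-6 draw, 36 - 10.6 = 25.4% or 51 - 16.3 = 34.7% remain, about 25 or 34 events.

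**The case against.** The strongest answer is that there is hardly a conflict. The two sentences run in parallel, every enrolled patient has curative-intent surgery, and the natural reading is that the Abstract's treatment is the operation. The Methods are the operative text and give one definite date; an abstract only summarises. This largely stands. It reduces the mismatch to a minor inconsistency of wording, but does not remove it, because the eligibility criteria also use treatment for a course that is to be completed.

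A reader might infer more, and the documents do not support it:

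- *That the Abstract counts from the end of treatment.* It does not say so.
- *That sampling time is confounded with stage.* Enrolment runs from T1 to T4, with and without nodal disease, so unequal treatment length is plausible. But no adjuvant therapy, its length or its stage criteria are described for this cohort. For the Introduction's objective, confined to N0 patients, a contrast between node-positive and N0 patients does not arise.
- *That follow-up adds a third sampling anchor.* The Participation timeline does not time the draw.

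It is also fair to say that draw windows, the origin of the RFS clock and landmark rules are commonly left to the full protocol or analysis plan. Their absence here is not charged as a defect. Nor would a surgery anchor make the sample equivalent in all patients: anyone treated longer would be sampled sooner after finishing.

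**Conclusion.** The point holds in a limited form. The Abstract and the Methods use different words for the date of the second CTC/CTM draw. The text allows two dates for any patient treated beyond surgery, and the draw feeds an outcome listed as primary. Dependence on stage remains conditional. The difference between anchors, about 3-9 points more recurrences before the draw, rests on an assumed 2-4 month gap and a constant hazard, and concerns only an unstated fraction of patients.

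The consequence that does not depend on the anchor matters more. About 10.6-16.3% (10-16 of 97) would have recurred by month 6 if the cited 20-30% at 12 months applies with a constant hazard. An analysis of the second sample with RFS counted from treatment would include those recurrences. The article does not say that this will be done, so this is a hazard to close off rather than an error shown.

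**What to change.** Reconcile the Abstract and the Methods to one anchor for this research blood draw, and restate it in the primary outcome. The Methods already use surgery, a date that every enrolled patient has. Record the actual draw date for each patient.

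Analyse second-sample CTC/CTM against RFS as a landmark analysis: start the clock at the draw, include only patients recurrence-free at that time, and count only later recurrences. The pre-surgical sample can be analysed from the start, as it precedes all follow-up.

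The wording change and one recorded date cost almost nothing. Study status reports 27 patients recruited and mentions only pre-treatment CTC evaluation, so most second draws probably still lay ahead. Any already taken can be analysed at their true date. The real cost is statistical: patients who recur before the draw leave the second-sample analysis, so on the assumptions above it would rest on about 25-34 events instead of 35-49.

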## Introduction

Tumor metastasis is a major factor that leads to treatment failure and mortality. The cure for cancer metastasis is still challenging, so treating cancer effectively depend on our ability in arresting or preventing metastasis. Tumor mortality is a result of late diagnosis, so research into early detection is of greater importance in improving patient outcomes.

The WHO anticipates that by 2040, the global cancer burden will reach 27.5 million with approximately 16.3 million deaths.
^
1
^
^,^
^
2
^ In the WHO 2022 updates, oral squamous cell carcinoma is the 16
^th^ most common cancer globally, and the incidence of tongue cancer in persons younger than 45 years has increased worldwide.
^
3
^ One-third global burden of oral cancer is from India, tongue and floor of mouth comprise more than 50% of oral cancers.
^
4
^ The high tongue tumor prevalence in India demands scaling up relevant research in this area to deliver an optimal outcome. Recent data projecting a distressing trend in the recurrence and mortality rates of tongue cancers with increasing incidence in the non-habit associated tongue tumor.
^
5
^

Despite of advances in treatment modalities, the inability to control the metastatic process is one of the common reasons for treatment failures and high morbidity rates. Tumor metastasis is still not fully understood. Research may be of great importance to understand the tumor biology, heterogenicity, disease presentation and progression for tailoring accurate, affordable early detection tools and disease monitoring to interdict metastasis, thus survival outcomes.

Our primary objective of this study is the molecular profiling of tumor-free lymph nodes (N0) to assess the PMN changes and correlate them with recurrence -free survival in oral tongue squamous cell carcinoma patients.

The secondary objective is to evaluate the efficacy of CTC (circulating tumor cells) and CTM (circulating tumor micro emboli) in terms of relapse, and disease-free survival in N0 patients.

### Rationale of study

Tongue tumors are a matter of concern for oncologists, researchers and public health policymakers. Patients with tongue tumors have a higher proportion of treatment failures, even after standard treatment protocols. Treatment and clinical decisions on N0 neck in the early stages are still challenging. The primary goal is to investigate the early pre metastatic alterations even before a detectable metastasis and its association in initiating metastasis.

This study may help in
•Elucidating molecular metastatic driving events before or during early stages of metastatic colonization.•Identifying definite lymph node architecture parameters in predicting metastasis before tumor cells arrive.•Studying the significance of CTC/CTM occurring at early nodal-free tumors.

## Methods

### PMN trial design

The PMN study is designed as a prospective cohort observational study.

### Study settings

This study will take place at the Tertiary Care Advanced Centre (Department of Head & Neck Oncology & Pathology), Amrita Institute of Medical Sciences, Kochi (India).

### Trial registration

PMN CTC trial protocol registration has been done under the Clinical Trial Registry of India with registration number
CTRI/2022/03/041256 dated 22/03/2022. Patient accruals began in July 2022 and are projected to be concluded by July 2024. This protocol has been designed following the
SPIRIT 2013 Statement.

### Study population

The cohort will be adults aged 18-80 years, reporting to the Head and Neck Surgery department of Amrita Institute of Medical Sciences Kochi (tertiary care centre) with histopathological confirmed oral tongue squamous cell carcinoma who has not undergone any other treatment other than diagnostic biopsy, planned for curative intent surgery with neck dissection.

### Eligibility criteria

Eligibility criteria are summarised in
Table 1.

**Table 1. T1:** Inclusion & Exclusion Criteria.

Inclusion criteria	Exclusion criteria
Age- 18-80 years OTSCC patient reporting to this center without any previous tumour treatment history other than diagnostic biopsy.	Other subsites of oral squamous cell carcinoma.
Curative intent surgery as a primary modality of treatment with neck dissection.	OTSCC indicative of only wide local excision (not indicative of neck dissection).
T 1 to T4 with and without nodal metastasis and willing to sign the Informed Consent.	Secondary primary tumors or recurrent tumours.
Patients who agree to complete the treatment as per standard treatment protocol and routine follow-up visits.	OTSCC patients on neoadjuvant chemotherapy.

### Study condition (oral tongue squamous cell carcinoma-OTSCC)

Oral carcinoma commonly known as oral squamous carcinoma (OSCC) occurs as an ulcero proliferative lesion affecting any site starting from the lips to the oropharynx. OTSCC is the most common OSCC and often initiates at the flat thin squamous cells that line the surface of the tongue.
^
9
^ The aggressive biological behaviour and clinically unpredictable prognosis of tongue cancer with close affinity to the vascular lymphatic network necessitate the need for further research in this area.

### Study implementation/methodology

Patient inclusion is done based on the inclusion criteria. The trial will enroll 97 eligible patients. After obtaining written informed consent, blood samples and tissue biopsy blocks will be collected from them.

For CTC/CTM evaluation – Blood samples with minimum trauma will be collected before and 6 months after surgery. 5 mL of peripheral whole blood samples will be collected in 10-mL vacutainer tubes (Becton Dickinson, New Jersey). The blood samples will be stored in the refrigerator at 2 to 8
^0^ C. CTCs will be isolated by using Drugs Controller General of India (DCGI) approved OncoDiscover liquid biopsy technology. The OncoDiscover CTC isolation technique uses multifunctional, iron oxide-based, magneto-polymeric, and anti-epithelial cell adhesion molecule (EpCAM) targeting superparamagnetic nanoparticles.
^
10
^ Enumeration of CTC is based on CD45-, EpCAM+ and CK8,CK18 &CK19+ expression. CTM clusters are a group of two or more aggregated CTCs. The number of CTCs positive for PD-L1 expression is also evaluated.

### Immunohistochemistry (IHC) evaluation

Lymph nodes from these patients will be fixed and sectioned for routine histopathological evaluation. Formalin-fixed paraffin-embedded (FFPE) samples of the study may include T 1 to T4 with and without nodal metastasis. The lymph node samples will be grouped as Group A & B (
Figure 1) based on histopathological findings.

**Figure 1. f1:**
[figure not shown]
Trial Design of PMN Study.

The lymph nodes collected for analysis will include nodes without disease both in groups, where there is no nodal disease (-ve LN in NO) and those with nodal disease (-ve LN in N+). Also, will include lymph nodes with disease (LN+) and those with ECS (LN++). The molecular markers studied in the lymph nodes will be STAT 3, LOX 2, and VEGF A. IHC technique to be employed with primary and secondary antibody standardization protocol.

Group A: First echelon lymph nodes will be sampled in pathologic N0 (-ve node in NO).

Group B: In node-positive cases, - a normal uninvolved lymph node is taken just distal to the level of lowest positivity ie. if level 2 is involved, an uninvolved node from level 3 is taken (B1). The lymph nodes with positive disease (B2) and those with extracapsular spread (B3) will be included in the analysis when present.

To investigate the molecular characteristic features in the formation of premetastatic lymph nodes, selecting nonmetastatic LNs in the vicinity of metastatic LNs seems to be most suitable. Being taken from the same patient most of the other variables can be avoided.

The preparation of slides will be done in accordance with standard IHC techniques. Manual IHC with antigen retrieval in pressure cooker will be done. All antibody standardization will be done according to the company protocol manual. All stained slides shall be photomicrographed within 48 hours. Interpretation will be performed independently by two pathologists who were blinded to the other parameters of the subject. In cases of disparity, a third pathologist will be consulted and the best concordant result will be accepted for analysis. IHC slides will be graded according to staining intensity. The patients will be followed up as per the standard of care ie 2 monthly for the first year and 3 monthly in the second year. Clinical evaluation supplemented by imaging if needed will be used during follow-up. The overall survival, recurrence-free survival, locoregional, and systemic failure rates will be determined at the end of two years follow-ups.

### Primary outcomes

•The correlation of molecular expression of STAT 3, LOX 2, and VEGF in the premetastatic nodes (-ve N) with recurrence -free survival. These markers will be correlated individually. This will allow us to analyse the significance of premetastatic niche formation and the pathways leading to it.•To correlate the presence of CTC/CTM at two different time points to recurrence-free survival. This will allow us to establish the role of liquid biopsy in prognostication ie. the presence of CTC as a predictor/indicator of tumor spread via blood or lymphatic channels.•The evaluation of Stat3 expression in tissue and PD- L1 in CTC will reveal on the local and systemic immune status of patients respectively. Those PD-L -1positive CTCs may be a strong indicator of those exceptional CTCs that escape the immune surveillance mechanism.

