### Secondary outcomes

•The molecular markers for PMN will be compared in N0 and N+/N++ patients. This may allow a better understanding of the pathways of PMN formation. We expect to see the PMN changes be more prominent in the -ve N samples of N+/N++ patients.•Any architectural histopathologic feature which correlates with the PMN changes if identified will also help as a predictive marker.•To identify the role of CTC to predict PMN formation.

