### Statistical analysis plan

*Sample size calculation*

The sample size is determined by the formula,

n=(Z1−α22)pqd2
, z = Co-efficient of significance (1.96), α = Level of significance (5.0%),

p
= Prevalence of oral tongue tumour (50.0%)

q
 = 1-

p
 (50.0%), d = Desired precision (10.0%).

The minimum sample size for the study is computed and found to be 97 patients.

*Statistical method*

Chi-square Test to test the statistical significance of the association of the molecular expression (severity) of antibodies in lymph nodes and circulating tumor cells as numbers in oral tongue squamous cell carcinoma patients. To find the survival probability of disease-free survival, Kaplan Meier analysis and the comparison will be done using a log-rank test.

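### The protocol leaves open whether the primary marker–RFS analysis is pN0-only or also takes in node-positive patients; if combined, the log-rank test it names is confounded by nodal stage

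*Protocol article*

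**What the plan says.** All from the Protocol article.

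- **Introduction, primary objective:** "molecular profiling of tumor-free lymph nodes (N0) to assess the PMN changes", to be correlated with recurrence-free survival (RFS).
- **Eligibility criteria, Table 1:** patients enter as "T 1 to T4 with and without nodal metastasis and willing to sign the Informed Consent".
- **Text under Figure 1:** "The lymph nodes collected for analysis will include nodes without disease both in groups, where there is no nodal disease (-ve LN in NO"; the sentence goes on to add disease-free nodes from patients with nodal disease. Group A is a first-echelon node in pathological N0. Group B1 is an uninvolved node just beyond the lowest involved level in a node-positive patient.
- **Primary outcomes:** "The correlation of molecular expression of STAT 3, LOX 2, and VEGF in the premetastatic nodes (-ve N) with recurrence -free survival". Then: "These markers will be correlated individually". The outcome is not limited to N0 patients, and A is not separated from B1.
- **Secondary outcomes:** "We expect to see the PMN changes be more prominent in the -ve N samples of N+/N++ patients".
- **Statistical analysis plan, Statistical method:** a chi-square test for association, and for survival "Kaplan Meier analysis and the comparison will be done using a log-rank test". No strata, covariates or regression model are named.
- **Discussion:** lymph nodes are described as a decisive prognostic parameter across tumour types.

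**The concern.** The objective and the outcome do not clearly define the same patients. If the marker–RFS comparison runs across all patients with a sampled negative node, nodal stage sits behind both sides of it. The protocol predicts higher marker expression in node-positive patients and regards nodes as prognostic. Marker-high patients would then be disproportionately node-positive and would relapse more often for that reason alone.

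The sampled node also differs by stage: first echelon in A, a more distal level in B1. Expression could therefore vary with stage through sampling site as well as biology.

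At stake is what a positive primary result means. A significant combined log-rank test could reflect a premetastatic niche that predicts recurrence, or it could be pathological nodal stage seen through a marker. The stated method cannot tell these apart, and each of the three markers is exposed to the same problem.

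**Working it through.** **1. The plan's own figure.** n = z²pq/d² = 1.96² × 0.5 × 0.5 / 0.10² = 96.04, rounded up to 97. This reproduces. It is a precision figure for a proportion and gives no power for any survival comparison. I use n = 97 below.

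**2. Is B1 inside the primary outcome?** The outcome is set on negative nodes. The text under Figure 1 applies that label to uninvolved nodes in both N0 and N+ patients, and Secondary outcomes applies it again to N+/N++ patients. On the article's own vocabulary B1 is included. Only the N0 label in the Introduction points the other way.

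**3. Inputs for the size of the bias.** From the document: n = 97, two-year follow-up, two-sided 5%. The document gives no node-positive share, marker frequency or RFS by stage, so these are assumptions: 40% N+; N0 two-year RFS 80%; exponential times; and a marker with no effect within either stage.

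**4. Apparent hazard ratio, middle case** (marker-high in 30% of N0 and 60% of N+; N+ hazard ratio 2.5).
- Hazards: N0 −ln(0.80)/2 = 0.1116 per year; N+ 2.5 × 0.1116 = 0.2789.
- Two-year recurrence: N0 0.200; N+ 1 − 0.80^2.5 = 0.4276.
- Mean follow-up (recurrence/hazard): N0 1.793 years; N+ 1.533 years.
- Marker-high patients as shares of the cohort: N0 0.6 × 0.3 = 0.18; N+ 0.4 × 0.6 = 0.24. Events 0.18 × 0.200 + 0.24 × 0.4276 = 0.1386. Time 0.18 × 1.793 + 0.24 × 1.533 = 0.6906. Rate 0.2007.
- Marker-low patients: N0 0.42; N+ 0.16. Events 0.1524. Time 0.9981. Rate 0.1527.
- Ratio 0.2007/0.1527 = 1.31, from a marker with no effect within either stage.

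The same arithmetic gives 1.15 in the mild case and 1.73 in the strong case.

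**5. False-positive rate by simulation** (5,000 trials per case, n = 97):

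| Marker-high N0 vs N+ | N+ hazard ratio | Unstratified log-rank | Stratified by N0/N+ |
|---|---|---|---|
| 30% vs 50% | 2.0 | 7.2% | 5.4% |
| 30% vs 60% | 2.5 | 11.2% | 4.9% |
| 20% vs 70% | 3.0 | 34.0% | 4.5% |

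A repeat with a different random seed gave 7%, 12% and 33% unstratified, and 5% to 6% stratified.

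**6. Sensitivity.** A second grid varied the N+ share from 30% to 50%, with two-year recurrence of 20% vs 40% or 15% vs 45%. Unstratified rejection was 7–10% for marker-high 40% vs 60%, 12–26% for 30% vs 70%, and 22–50% for 20% vs 80%. Stratified rejection stayed at 4–6%. With equal marker frequency in both stages (50% vs 50%), the unstratified rate was 5%.

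**7. Precision in Group A alone.** 97 × 0.6 ≈ 58 patients; 58 × 0.20 = 11.6 events. With a 50:50 marker split:
- The standard error of log HR is about 2/√11.6 = 0.587. The 95% interval runs from HR ÷ 3.2 to HR × 3.2, since exp(1.96 × 0.587) = 3.16.
- Power is Φ(√(11.6/4) × ln HR − 1.96): 22% for HR 2 and 46% for HR 3.

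With N+ shares of 30% to 50%, the events are about 10–14 and the power 19–25% (HR 2) or 40–53% (HR 3).

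**The case against.** The strongest reply is that pooling is inferred. No sentence says Groups A and B1 are combined for RFS. The objective is labelled N0, A and B are defined as separate groups, and the N0 versus N+ marker comparison is a secondary outcome of its own. The text under Figure 1 describes which nodes are collected, which is not the same as an analysis set, and the figure itself is not visible. The log-rank sentence refers to disease-free survival and does not say which groups are compared. A condensed article may also leave strata and covariates to a fuller plan.

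Much of this stands. A reader might infer that the protocol prescribes an unstratified pooled test; it does not say so. A reader might infer that the markers will look prognostic; the documents support only that they can. A null marker is still non-significant in 66% to 93% of trials in the three main cases (100% − 34% and 100% − 7%), and nothing is inflated if the markers do not differ by stage. A reader might infer that the N0 question is lost; it is not, because Group A is identified separately and can be analysed.

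What does not fall away is the mismatch between the objective's label and the outcome's, both of which are in the article. Nor does the fact that the one survival comparison named carries no handling of nodal status, although the protocol itself predicts that the markers track stage. The article's remark that same-patient sampling removes most other variables helps the comparison of B1 with involved nodes in one patient. It does not help a comparison of RFS between patients.

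**Conclusion.** The point holds in conditional form. The article does not settle whether the primary marker–RFS analysis is pN0-only or includes B1. Its outcome wording favours including B1. If the groups are combined and compared by the log-rank test as named, the result is confounded by nodal stage.

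With 40% node-positive and 80% two-year RFS in N0, the error rate per marker is about 7% to 34% against a nominal 5%, with apparent hazard ratios of roughly 1.15 to 1.7 for a marker that does nothing within stage. More extreme splits take the rate to about 50%; equal marker prevalence takes it back to 5%. The direction follows from the protocol's own expectations. The size rests entirely on assumed stage mix, marker frequencies and recurrence rates.

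Stratifying by N0 versus N+ restores the nominal level in every case tried. A finer split that separates extracapsular spread was not examined, so these figures do not support it.

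**What to change.** 1. Name the analysis set once and use the same words in the Introduction objective and in Primary outcomes: pN0 only, or Groups A and B1 together.
2. If together, make the marker–RFS test a log-rank or Cox analysis stratified by pathological nodal status (N0 vs N+).
3. Report the Group A hazard ratio with its 95% confidence interval as the result that addresses the N0 objective, and report B1 separately.
4. Label any unstratified pooled Kaplan-Meier curve descriptive.

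The cost is wording: nodal status already defines the groups, so no new data are needed. According to Study status, 27 patients had been recruited and IHC evaluation of the nodes had not begun, so at that point the rule could be set before any marker result was known. The drawback is precision. With about 12 events in Group A under these assumptions, the interval will be wide, and the result should be presented as an estimate and not as a powered test.
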